#### Description of the laboratory tests

Laboratory testing is performed after transport to the collaborating Translational Biomarker Group, University of Geneva, Switzerland. The analysis focuses on the quantification of HFABP and NT-proBNP levels. Different immunoassays will be used to perform such measurements. These comprise commercial multiplex assays (H-FABP and NTproBNP R-Plex from Meso Scale Diagnostics, MSD), as well as a duplex Point-of-Care test (LVOCheck from ABCDx SA) developed within this project. Furthermore, samples can additionally be used to validate new POCTs that may be developed within this project or tested for additional biomarkers not yet defined at time of sampling.

The data obtained from both biomarkers, together with clinical parameters recorded from the subjects enrolled in the study, will be used to train and enhance an algorithm designed to predict the presence of LVO in subjects with stroke symptoms.

### Documentation of clinical data

Collection of additional clinical data is obtained from MSU treatment documentation (including clinical neurological deficits and NIHSS) as well as by requesting the treatment documentation and doctors’ letters from the hospitals providing information on further treatment and final diagnosis and is documented after pseudonymization.

### Data storage and management

All collected clinical data of the patients are pseudonymized by assigning a unique identification number. This pseudonym is assigned by the Charité data trust office (CHA-THS). Each study site maintains a pseudonymization list in which the patient identification numbers are linked to the full names and date of birth of the participants. This list serves the purpose of later identification of participants. It will be kept confidential and must not leave the study center. It will be archived for at least 10 years after the end of the study. In addition, participation in the study is noted in the patient file. Pseudonomyzed study data are collected in an electronic case report form (eCRF) and managed using Research Electronic Data Capture (REDCap) electronic data capture tools hosted at Charité—Universitätsmedizin Berlin (23, 24).

### Definitions

#### Ischemic stroke

An episode of neurological dysfunction caused by focal cerebral, spinal, or retinal infarction, while infarction is brain, spinal cord, or retinal cell death attributable to ischemia, based on pathological imaging or clinical evidence of cerebral, spinal cord, or retinal focal ischemic injury based on symptoms persisting ≥24 h or until death, and other etiologies excluded (25).

#### Large-vessel occlusion

Occlusion of blood vessels supplying the brain, detectable by angiography.

#### Intracerebral hemorrhage

Rapidly developing clinical signs of neurological dysfunction attributable to a focal collection of blood within the brain parenchyma or ventricular system that is not caused by trauma (25).

#### Stroke mimic

Certain diseases like syncope, epileptic seizure, hypoglycemia, hyperglycemia, migraine aura, dissociative disorder etc. that can cause similar symptoms as stroke. A stroke is initially clinically suspected, but the diagnostic criteria of stroke are not fulfilled (25).

### Statistics

#### Sample size estimation

From internal STEMO data, we know that approximately 14.4% of STEMO patients with stroke alerts have an LVO diagnosis (preliminary study: 260 LVO of 1800 stroke patients). If 800 patients with stroke alarms are included in the study, we can expect about 116 patients to have an LVO diagnosis.

If data from 800 patients are included in the analysis, it is possible to determine a 95% confidence interval for sensitivity ranging from 66.8 to 83.3% if the observed sensitivity is 75%. This confidence interval was calculated using the Clopper-Pearson method and is based on the assumption of a prevalence of LVO of 14.4%. Similarly, with data from 800 patients, it is possible to determine a 95% confidence interval for specificity ranging from 93.3 to 96.7% if the observed specificity is 95%.

Table 1 shows the values for the confidence interval limits in the case of other observed sensitivity and specificity measures.

**Table 1 tab1:** 95% confidence intervals for sensitivity and specificity assuming a prevalence of LVO of 14.4% and including data from 800 patients.

Sensitivity	95% confidence interval
65%	56.0–74.1%
70%	61.3–78.7%
75%	66.8–83.3%
80%	72.3–87.7%
Specificity	95% confidence interval
80%	77.0–83.0%
85%	82.3–87.8%
90%	87.7–92.3%
95%	93.3–96.7%

Sample size estimations were performed using nQuery Advisor 8.0 [nQuery (2017). Sample Size and Power Calculation. “Statsols” (Statistical Solutions Ltd), Cork, Ireland].

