### Hypotheses

#### Primary study hypothesis

As primary study hypothesis, we postulate that the measurement of the two previously identified biomarkers H-FABP and NT-proBNP in patients suspected of having an acute stroke will allow the identification of patients with large vessel occlusion with a specificity of at least 93% and a sensitivity of at least 66%.

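### The planning intervals in the text and Table 1 are not the Clopper-Pearson limits they are said to be; every printed lower limit is slightly too high

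*Protocol article*

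**What the plan says.** Under Sample size estimation, the protocol takes from internal data that "approximately 14.4% of STEMO patients with stroke alerts have an LVO diagnosis (preliminary study: 260 LVO of 1800 stroke patients"), and concludes for 800 patients that "we can expect about 116 patients to have an LVO diagnosis". For an observed sensitivity of 75% it gives an interval "ranging from 66.8 to 83.3% if the observed sensitivity is 75" per cent, and states the method: "This confidence interval was calculated using the Clopper-Pearson method and is based on the assumption of a prevalence of LVO of 14.4" per cent. It then says that the specificity interval is obtained similarly, "ranging from 93.3 to 96.7% if the observed specificity is 95" per cent. Table 1 adds three further observed values each for sensitivity and specificity, at the same prevalence and total.

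The primary study hypothesis sets the targets, identification of large-vessel occlusion (LVO) "with a specificity of at least 93% and a sensitivity of at least 66" per cent. The section gives no power calculation and no other precision target for the 800.

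**The concern.** Above 50%, a Clopper-Pearson interval has its longer arm below the estimate. The printed intervals do not. Their arms (below/above, in points) are 9.0/9.1, 8.7/8.7, 8.2/8.3 and 7.7/7.7 for sensitivity, and 3.0/3.0, 2.7/2.8, 2.3/2.3 and 1.7/1.7 for specificity. They are equal apart from rounding, so the stated method and the printed numbers cannot both be right.

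These intervals are the only precision argument given for the sample size, and the two shown in the text have lower limits just above the 66% and 93% targets. A reader who compares them with the targets sees more clearance than the named method gives. If the final analysis uses Clopper-Pearson, an observed 75% will also give a lower limit visibly below the published one.

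**Working it through.** **Inputs (Sample size estimation).** N = 800; LVO prevalence 14.4% (260/1800 = 14.44%); two-sided 95% Clopper-Pearson; observed values as in Table 1.

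**Denominators: these reproduce.** 800 × 0.144 = 115.2 and 800 × 260/1800 = 115.6, in line with the protocol's figure of about 116. That leaves 684 to 685 patients without LVO.

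**Formula.** With x = n·p: lower = Beta(0.025; x, n − x + 1), upper = Beta(0.975; x + 1, n − x). Where n·p is not a whole number, the formula is evaluated at the fractional x. At n = 116, 75% is exactly 87 patients.

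**Sensitivity (%)**

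| Observed | Printed | Exact, n = 115 | Exact, n = 116 | Printed lower limit too high by |
|---|---|---|---|---|
| 65 | 56.0–74.1 | 55.55–73.66 | 55.59–73.62 | 0.41–0.45 |
| 70 | 61.3–78.7 | 60.75–78.19 | 60.79–78.16 | 0.51–0.55 |
| 75 | 66.8–83.3 | 66.07–82.60 | 66.11–82.57 | 0.69–0.73 |
| 80 | 72.3–87.7 | 71.52–86.88 | 71.56–86.85 | 0.74–0.78 |

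**Specificity (%)**

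| Observed | Printed | Exact, n = 684 | Exact, n = 685 | Printed lower limit too high by |
|---|---|---|---|---|
| 80 | 77.0–83.0 | 76.80–82.94 | 76.81–82.93 | 0.19–0.20 |
| 85 | 82.3–87.8 | 82.10–87.59 | 82.10–87.59 | 0.20 |
| 90 | 87.7–92.3 | 87.50–92.14 | 87.51–92.14 | 0.19–0.20 |
| 95 | 93.3–96.7 | 93.09–96.51 | 93.09–96.51 | 0.21 |

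The printed upper limits are too high as well, by about 0.4–0.8 points for sensitivity and 0.1–0.2 for specificity. The intervals are displaced rather than narrowed: at 75% the exact width with n = 116 is 82.57 − 66.11 = 16.46 points, against 83.3 − 66.8 = 16.5 printed.

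**Could another denominator explain it?** No. Over n = 95–134 for LVO, no Clopper-Pearson fit to the four sensitivity rows has a maximum deviation below 0.82 points. Over n = 600–800 for non-LVO, none is below 0.21 points.

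**Where might the numbers come from?** Placing the exact half-width symmetrically around the estimate fits all rows within 0.07 points at n = 115 and 685. It does not match every limit at one decimal: 75 ± 8.27 (n = 115) gives 66.73–83.27, and 66.73 rounds to 66.7, not 66.8. Rounding the full width to 0.1 first and then halving it matches 15 of the 16 limits. Other methods at the protocol's n do worse. Wald is too narrow (67.1–82.9 at 75%), Wilson is asymmetric (66.4–82.0 at 75%), and Wald with continuity correction gives 61.2–78.8 at 70%.

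**Distance from the targets.** Sensitivity 75%: printed 66.8 − 66 = 0.8; exact 66.07 to 66.11 − 66 = 0.07 to 0.11. Specificity 95%: printed 93.3 − 93 = 0.3; exact 93.09 − 93 = 0.09.

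**The case against.** The best defence is that Table 1 is a planning illustration. Its widths, which are what a precision argument rests on, are essentially right. The limits move by less than a point, and at 75% and 95% they stay above the targets. The study's reported intervals will come from the data. All of this stands, and it limits the weight of the point. It does not remove the contradiction between the named method and the printed numbers.

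Three stronger readings are tempting, and the protocol does not support them.

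- **That an observed sensitivity above 75% is needed.** With 115 LVO patients, 86/115 (74.8%) has a lower limit of 65.8%, and 87/115 (75.7%) is the first count to clear 66%. But that threshold depends on taking 115. At the protocol's own figure of about 116, 87/116 is exactly 75.0% and gives 66.1%.
- **That the study is unlikely to meet its targets.** The hypothesis states target values, but nowhere does the protocol require a lower confidence limit to exceed them. A probability of success would assume a rule that is not there. It would also assume a fixed cut-off, whereas the analysis section tunes the cut-off on the data.
- **That the re-centring is established.** It is inferred from the numbers. Wald with continuity correction at n of about 117 to 118 fits the sensitivity rows almost as well. The mismatch with Clopper-Pearson holds whichever cause is right.

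**Conclusion.** The point holds as an error in stated figures. The two intervals in the text and all eight rows of Table 1 are not Clopper-Pearson limits for 800 patients at 14.4% prevalence. The printed lower limits are too high by about 0.4–0.8 points for sensitivity and about 0.2 points for specificity. The apparent clearance of 0.8 and 0.3 points over 66% and 93% becomes about 0.1 point each.

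The result rests only on the protocol's inputs and its named method. Taking 115 or 116 LVO patients, or 684 or 685 without LVO, changes the last printed digit by at most 0.1.

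A reader might infer that 800 patients is too few. The documents do not support that: the exact lower limits at the two planning values still exceed the targets, the interval widths hardly change, and no lower-limit criterion is stated. This is a small correction, but it concerns the only precision basis given for the sample size.

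**What to change.** Replace the two intervals in the text and the eight rows of Table 1 with exact Clopper-Pearson limits, and state the LVO and non-LVO denominators used:

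- Sensitivity: 65%: 55.6–73.6; 70%: 60.8–78.2; 75%: 66.1–82.6; 80%: 71.5–86.9.
- Specificity: 80%: 76.8–82.9; 85%: 82.1–87.6; 90%: 87.5–92.1; 95%: 93.1–96.5.

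The last digit can differ by up to 0.1 with the denominators chosen. If a different interval method was intended, name it and print its limits instead.

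The cost is two sentences and eight table rows. The stated lower limits become slightly less favourable; neither the sample size nor the conduct of the study changes.

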#### Statistical analysis

A detailed statistical analysis plan will be provided before the analyses of the data.

Descriptive statistical measures such as mean and standard deviation and median and inter quartile ranges will be reported.

##### Statistical analysis of the primary hypothesis

The definitive diagnosis for LVO (gold standard) results retrospectively from the information in the doctor’s letter. Multiple binary logistic regression is used for the algorithm to be developed to predict the individual probability of LVO. Dependent variable: definitive LVO diagnosis from the doctor’s letter, independent variables: Biomarkers H-FABP and NT-proBNP, age, gender, and other clinical parameters and symptoms that can be easily and quickly recorded. The primary outcome analysis yields to evaluate the additional diagnostic value of the biomarkers to clinical and patient characteristics. Since this an observational study, relevant characteristics, that are linked to the outcome will be incorporated in the model for the primary analysis. Using multiple regression models, it is possible to evaluate the additional impact of biomarkers on the outcome after including other patient charactertistics. The method for panel selection will largely follow the procedure outlined by Robin et al. (26), employing panelomics. In summary, we will determine the ideal cutoff values through iterative permutation-response calculations utilizing all relevant parameters (26). The cutoff value will be adjusted in 2% quantile increments, with the sensitivity assessed after each change. This process will continue until we reach peak sensitivity with a specificity of over 95%.

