### Outcomes

The aim of the collaborative project LVOCheck is to develop a cost-effective point-of-care test for rapid identification of patients with LVO. The LVOCheck test is intended to be performed prehospitally in regular ambulances so that patients can be transported directly to the nearest thrombectomy center for treatment. The main objective of the subproject LVOCheck-Opti is to evaluate if the measurement of two previously identified biomarkers, HFABP and NT-proBNP combined with clinical parameters, in patients with suspected acute stroke will allow the identification of patients with large vessel occlusion with high specificity and sensitivity.

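### The primary analysis is said to evaluate the biomarkers' added diagnostic value, but the only accuracy result it fixes is for the all-parameter algorithm, with no clinical-only rule at the same specificity

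*Protocol article*

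**What the plan says.** All places are in the protocol article.

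- **Purpose.** Statistical analysis of the primary hypothesis: "The primary outcome analysis yields to evaluate the additional diagnostic value of the biomarkers to clinical and patient characteristics".
- **Model.** The same section fits one multiple logistic regression for LVO. Its predictors are H-FABP, NT-proBNP and "age, gender, and other clinical parameters and symptoms that can be easily and quickly recorded".
- **Route to added value.** With multiple regression, "it is possible to evaluate the additional impact of biomarkers on the outcome after including other patient charactertistics". The section does not say in what measure that impact will be expressed.
- **Accuracy result.** Cutoffs are searched over all relevant parameters, in 2% quantile steps, "until we reach peak sensitivity with a specificity of over 95" percent.
- **Target.** Primary study hypothesis: identification of LVO "with a specificity of at least 93% and a sensitivity of at least 66" percent.
- **What is being judged.** The Primary study hypothesis and the Primary end point name the two biomarkers only. Aim of the study, Outcomes ("HFABP and NT-proBNP combined with clinical parameters, in patients with suspected acute stroke will allow the identification of patients") and the primary analysis add clinical parameters.
- **Severity data.** Documentation of clinical data lists the MSU records, "including clinical neurological deficits and NIHSS". NIHSS is therefore collected, but it is not named as a predictor.

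No section names a clinical-only model, a comparison at matched specificity or a paired difference in sensitivity. A detailed statistical analysis plan is announced and is not shown.

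**The concern.** The stated purpose is a difference: what the blood test adds to what is already known about the patient. The accuracy result is a level: how well everything together performs against a fixed target. A level cannot show a difference without a comparator.

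The regression route does address the difference, but on another scale. A biomarker coefficient or a model-comparison test shows whether the biomarkers carry information about LVO beyond the clinical variables. It does not show how many more LVO patients are detected at the specificity required. At a cutoff far out in the tail of the non-LVO distribution, a clearly significant term can move very few patients across the line.

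The results are to train the algorithm of a point-of-care device meant for regular ambulances, where symptoms that can be recorded quickly are available without a blood test. The case for the device rests on the increment in detection.

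**Working it through.** **Inputs from the article.** N = 800, LVO prevalence 14.4% (260 of 1800), about 116 LVO cases expected, target 66% sensitivity and 93% specificity, cutoff search at specificity over 95%.

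**Inputs assumed.** The article gives no clinical-only performance and no biomarker effect size. Scores are taken as normal with unit variance in LVO and non-LVO patients, with means *d* SD apart, and the biomarker as independent of the clinical score.

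**Step 1. The article's own figure.** 800 × 0.144 = 115.2 and 800 × 260/1800 = 115.6. The stated 116 reproduces, leaving 684 non-LVO patients.

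**Step 2. Gain on the endpoint scale.** Sensitivity at specificity *s* is Φ(d − z_s), with z_0.95 = 1.645 and z_0.93 = 1.476. AUC = Φ(d/√2). Adding an independent biomarker with shift d_b gives d = √(d_clin² + d_b²). Take d_clin = 1.6.

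| Biomarker shift | Combined d | AUC | Sensitivity at 95% specificity | Gain (points) |
|---|---|---|---|---|
| none | 1.600 | 0.871 | 48.2% | – |
| 0.3 SD (OR 1.35) | 1.628 | 0.875 | 49.3% | 1.1 |
| 0.4 SD (OR 1.49) | 1.649 | 0.878 | 50.2% | 2.0 |

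**Step 3. What the regression would show in the same cases.** Simulating 116 LVO and 684 non-LVO patients and fitting the clinical score and biomarker jointly by logistic regression, the biomarker term is significant at the two-sided 5% level in about 70% of runs (0.3 SD) and 91% (0.4 SD). The shortcut Φ(d_b·√(116 × 684/800) − 1.96) gives 85% and 98%. It ignores the information lost by adjusting for a strong clinical score, so it is too high.

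**Step 4. Uninformative biomarkers.** In simulations with zero biomarker shift, N = 800 and 14.4% prevalence, the likelihood-ratio test was significant in about 5% of runs, as it should be.

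**Step 5. When clinical data alone would meet the target.** The condition is d = z_s + z_0.66, with z_0.66 = 0.412.

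- At 93% specificity: d = 1.476 + 0.412 = 1.888, so AUC = Φ(1.888/√2) = 0.909.
- At 95% specificity: d = 1.645 + 0.412 = 2.057, so AUC = Φ(2.057/√2) = 0.927.

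Across a range of clinical AUC, clinical-only sensitivity at 95% specificity is 43% (AUC 0.85), 57% (0.90), 67% (0.93) and 75% (0.95).

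**Step 6. Precision of a paired comparison.** With cutoffs held fixed, the 95% half-width is about 1.96·√(ψ/116), where ψ is the share of LVO patients whom the two rules classify differently.

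- ψ = 10%: 5.8 points
- ψ = 20%: 8.1 points
- ψ = 30%: 10.0 points

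Power of a paired (McNemar) test with 115 cases is Φ((δ√n − 1.96√ψ)/√(ψ − δ²)).

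- For a gain δ of 10 points: 80%, 67% and 50% at ψ = 15%, 20% and 30%.
- For a gain of 5 points: between 39% (ψ = 10%) and 16% (ψ = 30%).

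**The case against.** **Added value is not ignored.** The article plans to assess the biomarkers after including other characteristics. That wording is compatible with comparing models with and without them, and nothing confines it to an odds ratio or a p-value. Step 4 shows that such an assessment would not credit wholly uninformative biomarkers. This stands, and it narrows the point to the scale on which added value is measured.

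**The rest may be in the analysis plan.** A condensed article may leave much to that document, and the comparison may be specified there. That also stands as a possibility. However, the article is not silent here. It states the purpose, an accuracy procedure and a route to added value, and those as written do not give the purpose on the endpoint's scale. The Discussion itself cites a study that compared a biomarker plus NIHSS with NIHSS alone.

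**A stronger reading.** A reader might infer that clinical severity alone could produce a positive result and that the trial would then credit the blood test. The documents do not support this as it stands, for three reasons.

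- The primary hypothesis and primary end point name the biomarkers only. Under that wording clinical variables cannot produce the result.
- NIHSS is collected but is not a named predictor.
- The scenario needs a clinical AUC of about 0.91 to 0.93. In the illustration of step 2 every sensitivity at 95% specificity is 48% to 50%, so the 66% target would be missed with or without the biomarkers.

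**Conclusion.** The point holds in limited form. The primary analysis is assigned the question of added diagnostic value, and what the article fixes answers it as association, not as gain in sensitivity at the required specificity. The two can diverge: under the assumptions of step 2, significance is likely (about 70% or 91%) while the gain is 1.1 or 2.0 points. These effect sizes, normality and independence are assumptions; the illustration shows that divergence is possible, not that it will occur.

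If the algorithm includes clinical parameters, meeting 66%/93% does not by itself show a biomarker contribution, because clinical data alone would suffice at an AUC of about 0.91 (93% specificity) or 0.93 (95% specificity). Whether it includes them is unclear, since the hypothesis and end point sections differ from the aim, outcomes and analysis sections, and these must be reconciled. It does not follow that a purely clinical result would be passed off as a biomarker result, because the planned adjustment guards against that.

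**What to change.** In Statistical analysis of the primary hypothesis:

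1. Add a clinical-only rule, built with the same algorithm and cutoff procedure as the combined rule and set to the same target specificity.
2. Report the paired difference in sensitivity (combined minus clinical-only) with a bootstrap 95% interval that repeats the cutoff tuning in each resample.
3. Report the likelihood-ratio test and the AUC difference alongside it.
4. Base any statement about the biomarkers' added value on this estimate and its interval. Do not make it a new pass/fail test: with power of 16% to 39% for a 5-point gain, such a test would often fail for lack of LVO cases.
5. Reconcile the Primary study hypothesis and Primary end point with Aim of the study, Outcomes and the primary analysis, so that it is clear whether the 66%/93% target applies to the biomarkers alone or to the biomarkers with clinical parameters.

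The cost is one more model fit on data already collected, and some wording. The drawback is precision: with about 116 LVO cases the interval is roughly ±6 to 10 points before allowing for cutoff tuning, so a small gain may be inconclusive.

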**Methods and analysis:**

We plan a multicenter prospective observational study with 800 patients with suspected stroke enrolled within 24 h of symptom onset. Study participants will be recruited at three sites (MSUs) in Berlin, Germany. Blood-samples will be taken pre-hospitally at the scene and tested for HFABP and NT-proBNP levels. Additional clinical data and information on final diagnosis will be collected and documented in an electronic case report form (eCRF). Sensitivity and specificity of the combination will be calculated through iterative permutation-response calculations.

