## Methods and analysis

### Aim of the study

The LVOCheck-Opti study aims to demonstrate that patients with large vessel occlusion can be identified with at least 93% specificity and 66% sensitivity by measuring two blood biomarkers previously identified in acute stroke patients, H-FABP and NT-proBNP, in conjunction with clinical parameters (21, 22). This is achieved by testing biomarker levels in a very early time window in patients suspected of having a stroke when queried by the dispatch center, regardless of the final diagnosis. The approach taken in the present study to detect LVO is based on data from other previously unpublished studies, for example, Biofast 1 and Biofast 2,^1^ presented at ESOC 2021.^2^

The results will be used to train and optimize the test algorithm used in the LVOCheck POCT (point of care test) device. Subsequently, the device will be evaluated in prehospital use in a study independent of LVOCheck-Opti.

As neuronal cell injury quickly progresses with time after onset, we also expect to find an increase in sensitivity and specificity over time. Most studies examine blood samples drawn at a far later stage after AIS, therefore the dynamic course of biomarker levels in the very early stages of stroke is mostly unknown.

Furthermore, we seek to determine the main diagnosis of false positives. We assume that most patients with a false positive test result suffer from AIS without LVO and not from hemorrhagic stroke or stroke mimic. This would consequently result in a transport and treatment strategy optimized for patients with AIS.

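### The cut-off search admits only rules with specificity above 95% in the same 800 patients used to demonstrate 93%/66%, so the specificity half cannot fail on the observed value and sensitivity is biased upward

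*Protocol article*

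**What the plan says.** The protocol article gives this study two tasks.

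- **Demonstration.** Under 'Aim of the study', it "aims to demonstrate that patients with large vessel occlusion can be identified with at least 93% specificity and 66% sensitivity". The primary hypothesis repeats this as a claim that measuring the markers "will allow the identification of patients with large vessel occlusion with a specificity of at least 93% and a sensitivity of at least 66" per cent. Sensitivity and specificity are the primary end point.
- **Development.** The same aim section adds: "The results will be used to train and optimize the test algorithm used in the LVOCheck POCT (point of care test) device".

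The section on analysing the primary hypothesis describes an algorithm not yet built. It is a logistic regression on the two biomarkers, age, gender and an open list of quickly recorded clinical items, followed by panel selection and a cut-off search in 2% quantile steps. The search ends as follows: "This process will continue until we reach peak sensitivity with a specificity of over 95" per cent. The abstract makes the search the source of the primary figures: "Sensitivity and specificity of the combination will be calculated through iterative permutation-response calculations".

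The sample size section bases precision on the full cohort: "If 800 patients with stroke alarms are included in the study, we can expect about 116 patients to have an LVO diagnosis". It gives binomial intervals for both measures.

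**The concern.** A performance claim can be tested only if the data are able to contradict it. Here the acceptance rule (above 95%) is stricter than the target (93%) and is applied to the same patients. Observed specificity therefore reflects the rule and says nothing about the markers.

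The rule then takes the highest sensitivity that remains. A maximum over many candidate panels and cut-offs exceeds, on average, what the chosen rule achieves in new patients. The binomial intervals in the sample size section suit a test fixed in advance and do not allow for this search.

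At stake are the credibility of the primary conclusion and the expectations carried into the device study, which inherits cut-offs set here.

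**Working it through.** **Inputs from the article.** N = 800; LVO prevalence 14.4% (260/1800); targets 93% and 66%; search constraint above 95%; 2% quantile steps; Clopper-Pearson intervals. The number of candidate predictors and the true separation between LVO and non-LVO are not given, so they are assumed below.

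**1. The plan's own figures.** 800 × 260/1800 = 115.6, hence about 116 LVO; 800 × 0.144 = 115.2 leaves about 685 non-LVO. Exact Clopper-Pearson limits are:

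- sensitivity 75%: 66.1 to 82.6% (stated 66.8 to 83.3%)
- specificity 95%: 93.1 to 96.5% (stated 93.3 to 96.7%)

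The stated limits match the observed value ± half the exact width to within about 0.1 point. The widths reproduce, but the limits have been re-centred by up to about 0.8 point.

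**2. Specificity half.** Exact lower limit = Beta quantile(0.025; x, n − x + 1).

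| Non-LVO patients (n) | Smallest count above 95% (x) | Observed | Exact lower limit |
|---|---|---|---|
| 685 | 651 | 95.04% | 93.13% |
| 570 | 542 | 95.09% | 92.98% |
| 550 | 523 | 95.09% | 92.94% |

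The observed value clears 93% at any size. The lower limit also clears it at the planned size. Below roughly 600 non-LVO patients it can fall slightly short.

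**3. Sensitivity half.** Simulation with 115 LVO and 685 non-LVO patients and independent normal predictors, at most four of them informative, with total separation 2 SD. The rule was chosen in-sample at specificity above 95% and then applied to a large new sample (300 runs per logistic setting, 150 per threshold setting). The logistic cut-off was taken at the 95% boundary itself; the threshold panels used the 2% grid.

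| Assumed rule | Sensitivity in-sample | Sensitivity in new patients | Excess (points) | Specificity in new patients |
|---|---|---|---|---|
| Logistic, 5 predictors | 65.0% | 63.9% | 1.1 | 94.7% |
| Logistic, 10 | 66.5% | 63.9% | 2.7 | 94.5% |
| Logistic, 20 | 67.7% | 63.3% | 4.4 | 94.1% |
| Two-marker thresholds, 2 candidates | 58.4% | 55.0% | 3.4 | 94.5% |
| Two-marker thresholds, 8 candidates | 43.8% | 37.2% | 6.6 | 94.1% |

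(Excess was computed before rounding.) A separate simulation of a three-variable threshold panel (two biomarkers plus the best of six clinical variables) gave 72.3% in-sample and 64.6% in truth, an excess of 7.7 points.

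**4. Uninformative predictors.** With zero separation, the 93% specificity target was met in 100% of runs. In-sample sensitivity was only 7.8 to 11.8%, so no run met the joint hypothesis.

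**5. Margin at the planning case.** 87/116 = 75.0% has an exact lower limit of 66.1%. One fewer detected case, 86/116 = 74.1%, gives 65.2%. An excess of about one point uses up the margin over 66%.

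**The case against.** **The analysis plan may deal with it.** A detailed plan is promised, and the panel method follows a cited procedure that may contain internal validation. Silence on resampling in a condensed article would not be a finding, and a reader should not infer that uncorrected values will certainly be reported. What stands is what the article itself fixes: the search rule, the targets, and a primary result obtained through the search. As written, these conflict.

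**The development role is disclosed.** The article says: "Subsequently, the device will be evaluated in prehospital use in a study independent of LVOCheck-Opti". The two biomarkers are also named in advance. Both points limit the harm downstream. But the later study tests the device and does not supply evidence for this study's primary hypothesis, and the clinical variables, panel and cut-offs are still chosen on the data.

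**The effect on specificity is modest.** In the simulations specificity in new patients averaged 93.6 to 94.7%, still above 93%, and fell below 93% in 3 to 26% of runs (3 to 11% with informative predictors). This is fair. The defect is less a large bias in specificity than a claim that the data cannot refute.

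**The intervals are for planning, and no interval-based success criterion is stated.** This is also fair. The lower-limit results show scale and do not describe a decision rule in the article.

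**Conclusion.** The rule as written is wrong for the claim it serves. Observed specificity of at least 93% is guaranteed, and at the planned size so is an exact lower limit above 93%. Apparent sensitivity is biased upward. The direction is certain. The size depends on assumptions: about 1 to 3 points for the logistic score with 5 to 10 predictors, about 4 with 20, and about 3 to 8 for searched marker thresholds.

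Two stronger readings are not supported.

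- A reader might infer that any data set, even with useless markers, confirms the primary hypothesis. That holds for the specificity half only; the joint claim can fail on sensitivity, and with noise it did.
- A reader might infer a high general risk of false confirmation. One panel scenario gave 75% of replicates that met the targets in-sample but not in truth, but its true sensitivity (64.6%) lay just under 66%. A rerun with a similar three-marker panel gave 0% at a 1.0 SD shift per marker, 17% at 1.1, 85% at 1.3 and 10% at 1.5. The logistic runs above share this dependence: observed sensitivity reached 66% in 48%, 58% and 68% of runs (5, 10, 20 predictors) against 24%, 26% and 17% in truth, again with true values near the target.

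**What to change.** Choose one of two routes before the data are analysed.

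1. **Keep the claim and correct the estimate.** Repeat the whole procedure (predictor choice, panel choice, 2% cut-off search under the specificity constraint) inside repeated nested cross-validation or a full-pipeline bootstrap. Make the optimism-corrected sensitivity and specificity, with bootstrap intervals, the primary result, and judge 66% and 93% on them. Label in-sample values as apparent performance.
2. **Present the study as development only.** Drop the wording about demonstrating 93%/66%, report apparent performance as such, and leave the claim to the later independent study.

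The first route costs analysis-plan wording, computing time and slightly less favourable figures. The second costs wording and the confirmatory claim. Neither needs additional patients.
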